### Statistical analysis

The sample size calculation is based on the primary outcome of determining a difference in cardiovascular outcomes between patients receiving LT4 or not. The TRUST study of 737 patients aged 65 years and older found a cardiovascular outcome rate of 4.9% in the treatment group and 5.4% in the placebo group. Therefore, based on these outcome rates, for the cohort study, the minimum sample size required is 82,118 patients. Of this sample, 41,059 patients will be prescribed LT4 and 41,059 patients will not be prescribed LT4. A matching ratio of 1:4 (treatment: no treatment) will be used for the target trial emulation study. Therefore, the sample size required is 129,020 patients, with 25,804 patients prescribed LT4 and 103,216 patients not prescribed LT4. This sample size provides a power of 0.9 and alpha of 5%. In both studies, if missing data occurs, multiple imputation methods will be used if up to 40% of the data is missing [47]. Otherwise, pairwise deletion will be used.

In the target trial emulation study, the causal contrasts of interest will be intention-to-treat effect. Chi-square analysis will be used to compare the categorical characteristics of the participants in both studies, such that a p-value of less than 0.05 will be considered significant. Descriptive statistics will be presented. In both studies, the frequency of hypothyroidism diagnosis, smoking status, sex, ethnicity, and location will be given for each group. Survival analysis methods, including Cox proportional hazard models and Kaplan-Meier curves, will be fitted to compare the time to outcome between the groups. The hazard ratios with their 95% confidence intervals will be given.

Confounding bias, immortal time bias, and information bias will be adjusted for both the cohort and target trial emulation studies [48]. In addition, selection bias and attrition bias will be adjusted for in the target trial emulation study. Confounding factors include sex, BMI, co-morbidities, and smoking status. The adjustment for confounding factors will be done using inverse probability weighting in the target trial emulation study [49]. In both studies, subgroup analysis will be done for each cardiovascular and bone health outcome and each age group (51–60, 61–70, 71–80, 81–90, 91 + years). A subgroup analysis including patients with a TSH level between 4 0.0 mIU/L and the upper limit of their age range in the TEARS study will be carried out. Another subgroup analysis of patients who have had a TSH level of 10 mIU/L or above or not will be conducted. Also, sensitivity analysis will be undertaken in both studies for different TSH thresholds, as the standard threshold can differ between laboratories. This study will perform a secondary analysis based on baseline fT4 levels, comparing patients with a low normal versus high normal levels (below and above median levels at baseline, respectively).

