Previous studies that addressed the link between cardiovascular outcomes and LT4 treatment have failed to find a conclusive outcome. A cohort study on 1,642 patients aged over 70 years found no difference in cardiovascular events between treated and untreated groups [24]. The Thyroid Hormone Therapy for Older Adults with Subclinical Hypothyroidism (TRUST) study, a double-blind randomised placebo-controlled parallel-group trial of 737 adults aged 65 years and older with SCH, found no association between LT4 use and cardiovascular outcomes (hazard ratio 0.89; 95% confidence interval 0.47–1.69) [25]. The TRUST group concluded that LT4 should not be routinely prescribed to older people with SCH. Pooled results of the TRUST study and another randomised control trial found no significant difference in the cardiovascular risk of patients treated with LT4 versus those untreated [26]. However, both randomised controlled trials were underpowered due to small sample sizes. Most studies in older populations have not shown a clear association between SCH and cardiovascular events in patients aged over 65. The effect of mild thyroid failure on cardiovascular health becomes less evident with increasing age [27]. There is need for further large-scale studies investigating the impact of LT4 on cardiovascular health in patients over 50, particularly those aged between 50 and 65 years.

It is accepted that patients with overt hypothyroidism should be prescribed LT4 due to the association between the untreated condition and increased morbidity and mortality [28, 29]. However, the treatment of SCH is unclear due to a lack of reliable evidence in the past [30]. Over-treatment with thyroid hormones harms health, including poorer cardiovascular outcomes, atrial fibrillation, fractures, and osteoporosis [27, 31, 32]. However, over-treatment is common in older people and is associated with a longer time on replacement therapy and increasing age [33–35]. The European Thyroid Association guidelines recommend that SCH patients be prescribed LT4 when symptoms are shown and a TSH level is above 10 mIU/L [23]. It is also recommended that LT4 doses are personalised according to age, co-morbidities, and life expectancy [6]. However, research proves that these recommendations are not always followed [33].

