The current research group has completed a National Institute for Health and Care Research (NIHR) Research for Patient Benefit study (Study of Optimal Replacement of Thyroxine in ElDerly (SORTED) – a feasibility study: Ref: PB-PG-0610-22139) and has demonstrated that older people can tolerate a lower dose of LT4 and hence higher TSH levels [45]. The work done in 2016 explored the relationship between the three variables: diagnosis of hypothyroidism, TSH measurement, and LT4 treatment. A feasibility analysis at one large rural general practice in Northumberland, England, with a practice list size of 11,752 found that 465 patients had been diagnosed with hypothyroidism. The prevalence of hypothyroidism at the practice was 4%, and the highest prevalence was in the 81–90 years age category, at 9.85%. The female-to-male ratio with hypothyroidism at the practice was 4.4:1.0, such that 379 females had been diagnosed. Despite 465 patients diagnosed with hypothyroidism (Read Coded), 622 patients received treatment with LT4. This is an excess of 157 patients receiving LT4 without a diagnosis of hypothyroidism. This may represent a proportion of SCH patients that are not Read Coded as hypothyroid but are receiving treatment. It is also possible that a small proportion of these patients are hyperthyroid patients receiving block and replace treatment or patients with pituitary disorders. Alternatively, some patients may report symptoms suggestive of hypothyroidism but still have normal serum thyroid function tests and receive LT4 therapy in contravention of accepted clinical practice and guidelines. For this reason, our search strategy centres upon the TSH values recorded in the database rather than a diagnosis. Between 2003 and 2015, 215 (1.9%) patients were recorded as having an age-specific index TSH as mildly elevated, in line with the TEARS study. Of those, 39% were untreated, and 61% were treated with varying degrees of treatment length. This feasibility work concludes that 53% of the treated patients may have been over-diagnosed due to their TSH level being within the range of 4.0 mIU/L and the upper TSH limit given by the TEARS study [13].

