## Methods/Design

### Study aims

The study aims to evaluate whether LT4 benefits patients aged over 50 years with marginally raised TSH. The null hypothesis is that SCH patients over 50 years of age have the same bone health and cardiovascular outcomes when prescribed LT4 compared to those not prescribed LT4. The alternative hypothesis is that SCH patients aged over 50 years of age have worse bone health and cardiovascular outcomes when prescribed LT4 than those who are not prescribed LT4.

The objectives of the study are:

1) To use electronic healthcare records to undertake a cohort study comparing the cardiovascular outcomes (incident diagnosis of angina, myocardial infarction, stroke, peripheral vascular disease and stent/revascularisation procedure) between patients over 50 years of age with mildly elevated TSH levels prescribed LT4 versus those not prescribed LT4.

2) To use electronic healthcare records to undertake a cohort study comparing the bone health outcomes (incident diagnosis of osteoporosis, fragility fractures) between patients over 50 years of age with mildly elevated TSH levels prescribed LT4 versus those not prescribed LT4.

3) To use electronic healthcare records to undertake a cohort study comparing all-cause mortality outcomes between patients over 50 years of age with mildly elevated TSH levels prescribed LT4 versus those not prescribed LT4.

4) To use electronic healthcare records to undertake a target trial emulation study comparing the cardiovascular outcomes (incident diagnosis of angina, myocardial infarction, stroke, peripheral vascular disease and stent/revascularisation procedure) between patients over 50 years of age with mildly elevated TSH levels prescribed LT4 versus those not prescribed LT4 [46].

5) To use electronic healthcare records to undertake a target trial emulation study comparing the bone health outcomes (incident diagnosis of osteoporosis, fragility fractures) between patients over 50 years of age with mildly elevated TSH levels prescribed LT4 versus those not prescribed LT4.

6) To use electronic healthcare records to undertake a target trial emulation study comparing all-cause mortality outcomes between patients over 50 years of age with mildly elevated TSH levels prescribed LT4 versus those not prescribed LT4.

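### The emulation describes sustained LT4 strategies but names only an intention-to-treat contrast, and its 0.9 power holds for that contrast only if nobody switches

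*Protocol article*

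**What the plan says.** Four parts of the protocol article bear on this.

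- **Contrast (Statistical analysis).** "In the target trial emulation study, the causal contrasts of interest will be intention-to-treat effect". No other causal contrast is named for the emulation.
- **Strategies (Inclusion criteria).** Emulation patients are to begin LT4 and stay on it through a 5-year follow-up. Comparators are patients who receive no hormone replacement. The same item says that a strategy is assigned at baseline.
- **Sizing (Statistical analysis).** The rates come from the TRUST study, which "found a cardiovascular outcome rate of 4.9% in the treatment group and 5.4% in the placebo group". The Background describes it as "a double-blind randomised placebo-controlled parallel-group trial of 737 adults aged 65 years and older with SCH". For the emulation, "A matching ratio of 1:4 (treatment: no treatment) will be used for the target trial emulation study", giving 25,804 patients on LT4 and 103,216 not on LT4, at power 0.9 and alpha 5%. No allowance for later LT4 starting or stopping is stated.
- **LT4 use in practice (Background, feasibility work).** Among 215 patients with a mildly raised age-specific index TSH at one practice, 2003 to 2015: "Of those, 39% were untreated, and 61% were treated with varying degrees of treatment length".

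**The concern.** Starting LT4 and continuing it for 5 years, against no hormone replacement, is a pair of sustained strategies. An intention-to-treat contrast compares starting with not starting at baseline. A control who begins LT4 in year 2 still counts as a control, and an LT4 patient who stops still counts as treated. The two sections therefore describe different effects, and only the intention-to-treat one is named for analysis.

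Two things are at stake. The first is interpretation. If switching occurs, it pulls the intention-to-treat hazard ratio towards 1. A null could then mean that LT4 has no effect or that many controls were treated, and no named contrast tells these apart. That matters for a study whose Discussion expects implications for LT4 prescribing. The second is power. The 0.9 was computed at the whole placebo-trial difference, so it has no margin if the routine-care control arm comes to include treated patients.

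**Working it through.** **Step 1: reproduce the stated power.** Inputs from Statistical analysis: p1 = 0.049 (LT4), p2 = 0.054 (no LT4), n1 = 25,804, n2 = 103,216, alpha 5%. Sidedness is not stated; two-sided reproduces the plan's figures. For a two-proportion test with pooled null variance:

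power = Φ{[(p2 − p1) − 1.96 × SE0] / SE1}

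SE0 = √[p̄(1 − p̄)(1/n1 + 1/n2)], SE1 = √[p1(1 − p1)/n1 + p2(1 − p2)/n2]

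- p̄ = (0.049 + 4 × 0.054)/5 = 0.053
- SE0 = 0.001559, SE1 = 0.001517
- z = (0.005 − 1.96 × 0.001559)/0.001517 = 1.28, so power = 0.900

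Solving for size at 90% power gives 25,805 + 103,220 = 129,025, against the stated 129,020. The arithmetic is sound, and there is no spare power at that N.

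**Step 2: let part of control follow-up carry LT4 risk.** The documents give no rate, so the share c is an assumption. It is taken to move control risk in proportion: p2(c) = 0.054 − c × 0.005, with p1, n1 and n2 unchanged.

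| c (assumed) | Control risk | z | Power at 129,020 | N for 90% power |
|---|---|---|---|---|
| 0 | 5.400% | 1.28 | 0.90 | 129,025 |
| 5% | 5.375% | 1.12 | 0.87 | 142,600 |
| 10% | 5.350% | 0.96 | 0.83 | 158,480 |
| 20% | 5.300% | 0.64 | 0.74 | 199,545 |
| 30% | 5.250% | 0.32 | 0.62 | 259,285 |

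Here c is a share of control follow-up, not of control patients. If 20% of controls switch on average halfway through, c = 20% × 0.5 = 10% and power is 0.83. If 30% do so, c = 15% and power is 0.79.

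**Step 3: stopping in the LT4 arm.** With 10% of LT4 follow-up at the untreated risk (p1 = 4.95%) as well as c = 10% (p2 = 5.35%), power is 0.73. This may double-count, because the documents do not say whether the source trial's rates already include its own non-adherence.

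**Step 4: can one reading of the inclusion criterion remove the conflict?** There are two readings.

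- *The named contrast governs.* Later starters stay in the control arm and stoppers stay in the LT4 arm. The sustained-strategy effect is not estimated, and Step 2 applies.
- *The criterion restricts the arms to patients who stay on, or stay off, LT4.* Membership then depends on behaviour after baseline. That is not intention-to-treat, and it brings in the immortal time and selection bias that the plan says it will adjust for.

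Neither reading leaves both sections standing as written.

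**The case against.** The strongest reply has four parts.

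- **Intention-to-treat is legitimate and answers the objective.** Objectives 4 to 6 compare patients prescribed LT4 with those not prescribed it, and initiation against non-initiation is an ordinary answer to that wording. Objectives 1 to 3 put the same comparison to the cohort study. This stands. A reader might infer that the objective's comparison is never estimated; the documents do not support that. Only the sustained-strategy effect in the inclusion criteria lacks a contrast.
- **No loss of power is shown.** This also stands. A reader might infer that the stated power is not delivered, but there is no crossover rate in the documents. The figure is a required size and not a cap, and preliminary counts show 530,792 patients with TSH above 4 mIU/L. That count states no age limit or exclusions. A larger sample could restore power, but it would not separate no effect from treated controls.
- **The feasibility figures are not a switching rate.** Correct. The 61% is an ever-treated share from one practice over about 13 years. It shows that LT4 use of varying length occurs in such patients, not how many untreated patients start within 5 years. Reading 1:4 as a baseline prevalence of 20%, to derive later starters from the 61%, also fails: 1:4 is a matching ratio chosen by design.
- **Per-protocol details belong in a fuller document.** Partly right. Methods for a supplementary analysis may be left to an SAP. The article does fix the contrast and the strategies expressly, however, and the two disagree.

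**Conclusion.** The point holds as a conflict between two sections and an unstated condition on the power. The sustained LT4 against sustained no-LT4 effect, which the inclusion criteria describe, is not estimated by the emulation's only named contrast. The 0.9 is arithmetically right, but for intention-to-treat it holds only without switching. On assumed shares of 5% to 30% of control follow-up carrying LT4 risk, power at the stated size runs from 0.87 down to 0.62. Those figures rest on a true difference of 0.5 points, a two-sided 5% test and proportional mixing of risks. The actual loss cannot be computed from the documents, which do not establish that switching will be common.

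**What to change.** 1. **Reconcile Inclusion criteria and Statistical analysis.** For the intention-to-treat contrast, define the arms by LT4 initiation or non-initiation at baseline, without conditioning on later persistence.
2. **Add a per-protocol contrast for the sustained strategies.** Censor at deviation from the assigned strategy, with inverse-probability-of-censoring weights from time-updated TSH, fT4 and co-morbidities.
3. **Report LT4 uptake in the control arm and discontinuation in the LT4 arm** over the 5 years.
4. **Restate the emulation's power** as conditional on no switching, with a range over switching rates taken from THIN.

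The cost is wording and one additional weighted analysis. The planned extract largely covers it: LT4 start date, first and last recorded dose, current and past medications, dated thyroid tests and co-morbidity diagnosis dates. No LT4 stop date is listed, so it would have to be derived from the medication records. The stated power becomes less favourable. The per-protocol contrast will have wider intervals and must assume no unmeasured time-varying confounding.

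### At the planned sizes, a chi-square p<0.05 criterion for baseline characteristics flags trivial differences and does not measure balance in the weighted emulation sample

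*Protocol article*

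**What the plan says.** All the relevant text is in the protocol article, Methods/Design, Statistical analysis.

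- **Baseline comparison, both studies:** "Chi-square analysis will be used to compare the categorical characteristics of the participants in both studies, such that a p-value of less than 0.05" is treated as significant. Descriptive statistics are also promised, with group frequencies for hypothyroidism diagnosis, smoking status, sex, ethnicity and location.
- **Cohort size:** "for the cohort study, the minimum sample size required is 82,118 patients", split so that "41,059 patients will be prescribed LT4 and 41,059 patients will not be prescribed LT4".
- **Emulation size:** "A matching ratio of 1:4 (treatment: no treatment) will be used for the target trial emulation study", so that "the sample size required is 129,020 patients, with 25,804 patients prescribed LT4 and 103,216 patients not prescribed LT4".
- **Confounding:** sex, BMI, co-morbidities and smoking status are listed as confounders. Adjustment is by "inverse probability weighting in the target trial emulation study". No adjustment technique is named for the cohort study.

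**The concern.** A chi-square p-value combines the size of a difference with the number of patients. With more than 80,000 patients in each study, the second component dominates. Neither comparison is randomised, so small differences between treated and untreated patients are to be expected, and nearly all of them will pass the threshold. A table in which most rows are marked significant does not tell the reader which differences are large enough to matter for confounding.

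In the emulation there is a further mismatch. The estimate rests on the weighted sample, whereas an ordinary chi-square on participant counts describes the patients before weighting. Running the test on weighted counts would not cure the first problem, because the result would still depend on sample size. What is at stake is the reader's ability, and the study team's, to judge comparability in a study whose Discussion expects possible implications for prescribing.

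**Working it through.** **Step 1. Reproduce the planned sizes.** The plan uses a "cardiovascular outcome rate of 4.9% in the treatment group and 5.4% in the placebo group" and states "This sample size provides a power of 0.9 and alpha of 5" per cent. The calculation is for two proportions, two-sided, with pooled variance under the null and no continuity correction. At 1:1:

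n per arm = [1.960·√(2·p̄(1−p̄)) + 1.282·√(p₁(1−p₁)+p₂(1−p₂))]² / (p₁−p₂)², with p₁ = 0.049, p₂ = 0.054, p̄ = 0.0515.

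This gives 41,060 per arm (82,120 in total) against the stated 41,059 (82,118). The 1:4 version gives 25,805 + 103,220 = 129,025 against the stated 25,804 + 103,216 = 129,020. The differences are rounding, and power at the stated sizes is 0.900 in both studies. The sizes are sound on their own inputs and can be carried forward.

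**Step 2. Smallest difference that reaches p<0.05.** For a yes/no characteristic with prevalence p:

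- smallest difference = 1.96·√[p(1−p)(1/n₁ + 1/n₂)]
- standardised difference = that value / √[p(1−p)] = 1.96·√(1/n₁ + 1/n₂), which does not depend on p.

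Cohort: 1.96·√(2/41,059) = 1.96 × 0.00698 = 0.0137.

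Emulation: 1.96·√(1/25,804 + 1/103,216) = 1.96 × 0.00696 = 0.0136.

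In percentage points, for assumed prevalences (the article gives none):

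| Assumed prevalence | Cohort | Emulation |
|---|---|---|
| 5% | 0.30 | 0.30 |
| 10% | 0.41 | 0.41 |
| 20% | 0.55 | 0.55 |
| 50% | 0.68 | 0.68 |

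**Step 3. How the test behaves around that point.** It has 90% power at a standardised difference of (1.960 + 1.282) × 0.0070 ≈ 0.023 in both studies. A standardised difference of 0.02 gives p ≈ 0.004, and 0.05 gives p below 10⁻¹². A value of 0.1, a conventional balance limit that is not in the article, gives z = 0.1/0.00698 ≈ 14.3 in the cohort and 0.1/0.00696 ≈ 14.4 in the emulation. The significance threshold is therefore about one seventh of 0.1 (0.0137/0.1 ≈ 0.14). Differences of 0.02 and 0.1 receive the same label.

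**Step 4. Direction if the samples are larger.** The cohort figure is called a minimum. Study setting reports a preliminary 530,792 patients with TSH above 4 mIU/L, not stated to have had the eligibility criteria applied. Any larger sample lowers the threshold further.

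**The case against.** The strongest reply is that this is a descriptive baseline table and nothing more. Much of that stands, and it limits the point in several ways.

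- **Effect on estimates.** A reader might infer that the p-values decide which covariates are adjusted for, or that they undermine the emulation's causal estimate. The article does not say so. It lists the confounders separately, and no hazard ratio is said to depend on the chi-square results.
- **Missing diagnostics.** A reader might infer that the study has no check of weighted balance. A condensed article commonly leaves such checks to the full protocol or analysis plan, so their absence is not a finding. The point rests on the criterion that the article does state. The article also does not say which sample is tested; reading it as an ordinary test on participant counts is the natural reading, not an explicit statement.
- **Age bands.** A reader might infer that the test would miss serious imbalance in small age groups. The age bands are for subgroup analysis of outcomes, and no baseline tests within them are described.
- **Continuous variables.** The chi-square covers categorical characteristics only, but descriptive statistics are promised without that limit, and the plan groups age and TSH for its subgroup analyses. It would be too strong to say that these variables go unexamined.
- **Visible frequencies.** For the five characteristics to be reported by group, readers will see the size of the difference beside the p-value. That softens the problem for those rows but does not make the p-value informative.
- **Weighting.** It is named for the emulation only, so that part of the point does not extend to the cohort study.

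What remains is that the article fixes a significance threshold as its criterion, and at these sizes that threshold does not track imbalance.

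**Conclusion.** The point holds as a minor one about judging and reporting comparability. With 41,059 v 41,059 or 25,804 v 103,216 patients, chi-square p<0.05 is reached at a standardised difference of about 0.014, whatever the prevalence. An ordinary test on counts also does not measure balance in the emulation's weighted sample.

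The 0.014 follows from the stated sizes alone. The range of 0.41 to 0.68 percentage points rests on assumed prevalences of 10% to 50%, and the comparison with 0.1 rests on a convention from outside the document. The documents give no basis for saying that any effect estimate, interval or covariate choice is affected, and the sample size calculation is not in error on this point.

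**What to change.** Remove the p<0.05 criterion for baseline characteristics. In its place, report standardised differences for all baseline covariates, categorical and continuous, in both studies. In the emulation, report them before and after weighting. Set a limit in advance (0.1 is a conventional example, not a figure from the article), and state that if any covariate exceeds it after weighting, the weight model is re-specified before outcomes are examined.

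The cost is a change of a sentence or two, one extra balance table and possibly a re-fit of the weight model. No new data are needed.

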**Methods:**

This project includes a retrospective cohort analysis and a target trial emulation study using electronic patient records collected between 2006 and 2021 and recorded in The Health Improvement Network database. The primary outcome of this study is to compare the cardiovascular outcomes of subclinical hypothyroid patients aged over 50 years treated with levothyroxine compared to those untreated. Secondary outcomes are bone health and all-cause mortality outcomes. Descriptive and inferential statistics will both be employed to analyse the data. Secondary analysis will explore confounding factors, including age, sex, smoking status, body mass index, co-morbidities, and levothyroxine dosage.

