#### Inclusion criteria

Patients registered on the THIN database and aged over 50 on January 1st, 2006.Patients with a recording of TSH above 4.0 mIU/L between January 1st, 2006, and December 31st, 2021.Patients who are prescribed LT4 or receive no hormone replacement therapy. In the cohort study, patients in the treatment group will be prescribed LT4 before the end of the study period, December 31st, 2021. In the emulated target trial study, patients will initiate LT4 treatment and remain on it during a 5-year follow-up between January 1st, 2006, and December 31st, 2021. Patients in the emulated target trial study will be randomly assigned a strategy at baseline and be aware of their assignment.In the cohort study, patient follow-up ends at death, withdrawal from the database or December 31st, 2021, whichever occurs first.

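### In the cohort study, Kaplan-Meier curves for cardiovascular and bone outcomes censor deaths, so they would overstate risk if read as the proportion of patients who have an event

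*Protocol article*

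**What the plan says.** The Statistical analysis section of the protocol article names the methods for all time-to-event outcomes in one sentence: "Survival analysis methods, including Cox proportional hazard models and Kaplan-Meier curves, will be fitted to compare the time to outcome between the groups". The numerical result promised is the hazard ratio: "The hazard ratios with their 95% confidence intervals will be given".

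The Inclusion criteria section states: "In the cohort study, patient follow-up ends at death, withdrawal from the database or December 31st, 2021, whichever occurs first". Death thus stands beside withdrawal and the administrative end date as a reason to stop follow-up. For the target trial emulation the same section gives a 5-year follow-up but does not say how death is handled.

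Study aims defines the cardiovascular outcome as "incident diagnosis of angina, myocardial infarction, stroke, peripheral vascular disease and stent/revascularisation procedure" and the bone outcome as "incident diagnosis of osteoporosis, fragility fractures". Death is part of neither. It is an outcome of its own; the abstract says: "Secondary outcomes are bone health and all-cause mortality outcomes".

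Patients are over 50 at the start of 2006, and data run to the end of 2021, so cohort follow-up can last up to 16 years. The Statistical analysis section adds that "subgroup analysis will be done for each cardiovascular and bone health outcome and each age group", with bands up to 91 years and over. Date of death is among the variables listed in Study setting. The article does not mention competing risks or cumulative incidence.

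**The concern.** A Kaplan-Meier curve that censors deaths estimates what would be seen if nobody could die before having an event. For all-cause mortality this problem does not arise. For an incident diagnosis of angina, stroke or osteoporosis in an ageing population, patients who die first can never have the event, yet the curve treats them as if they still could. One minus Kaplan-Meier then lies above the real proportion affected.

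At stake is how the figures will be read. The Discussion names policymakers, NHS commissioning readers and the general practice press as audiences, and such readers are likely to take a curve as an absolute risk. The gap widens with follow-up time and with mortality, so it is greatest in the oldest patients.

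**Working it through.** **What the plan's own figures show.** The protocol gives no absolute risk from a curve, so no figure on this point can be reproduced. The only computed figures in the section are the sample sizes. With p1 = 0.049, p2 = 0.054, two-sided alpha 5%, power 0.9 and r untreated patients per treated patient, the treated group needs

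n = [1.960·√((1+1/r)·p̄(1−p̄)) + 1.2816·√(p1(1−p1) + p2(1−p2)/r)]² / (p1−p2)²,

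where p̄ = (p1 + r·p2)/(1 + r). For r = 1 this gives 41,060 per group (stated: 41,059). For r = 4 it gives 25,805 + 103,220 (stated: 25,804 + 103,216). These agree apart from rounding, and the present point does not change them.

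**Direction.** Let h be the event hazard and d the hazard of death without a prior event, both taken as constant.

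- One minus Kaplan-Meier, deaths censored: 1 − exp(−h·t)
- Proportion who have an event (cumulative incidence): h/(h+d) · [1 − exp(−(h+d)·t)]

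The second is smaller than the first whenever d > 0, so the direction needs no assumption about rates.

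**Size.** The protocol gives neither yearly event rates nor mortality. The values below are assumptions: h = 2% per year, with d varied widely.

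Worked example at 10 years, d = 5% per year:
- Kaplan-Meier: 1 − exp(−0.02·10) = 1 − exp(−0.20) = 18.13%
- Cumulative incidence: 0.02/0.07 · [1 − exp(−0.70)] = 14.38%
- Ratio: 18.13/14.38 = 1.26

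| Years | 1 − Kaplan-Meier | Deaths 1%/yr | Deaths 5%/yr | Deaths 10%/yr | Deaths 20%/yr |
|---|---|---|---|---|---|
| 5 | 9.52% | 9.29% (1.02) | 8.44% (1.13) | 7.52% (1.27) | 6.06% (1.57) |
| 10 | 18.13% | 17.28% (1.05) | 14.38% (1.26) | 11.65% (1.56) | 8.08% (2.24) |
| 15 | 25.92% | 24.16% (1.07) | 18.57% (1.40) | 13.91% (1.86) | 8.76% (2.96) |

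The death columns show cumulative incidence, with the ratio of one minus Kaplan-Meier to it in brackets. The ratio depends little on the assumed event hazard. At 10 years with deaths at 5% per year it is 1.27, 1.26 and 1.26 for event hazards of 1%, 2% and 3%. With deaths at 20% per year it is 2.28, 2.24 and 2.21.

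**Between groups.** Suppose both groups have h = 2% per year, with deaths at 4% per year in one and 5% in the other. At 10 years Kaplan-Meier shows 18.13% in both. Cumulative incidence is 0.02/0.06 · [1 − exp(−0.60)] = 15.04% against 14.38%, a difference of 0.66 percentage points.

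**The case against.** The strongest reply is that the protocol promises hazard ratios and no absolute risks. A Cox model that censors deaths estimates a cause-specific hazard ratio, a recognised target when the question is whether levothyroxine itself affects these outcomes. This stands. A reader might infer that the primary comparison is biased or that the hazard ratios are inflated; the documents do not support that. The harm arises only when the curves are read as risks.

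A second strong reading is that the curves misrepresent the difference between groups. In the example above, Kaplan-Meier correctly shows equal event hazards, while cumulative incidence answers another question: how many patients in each group have an event. The protocol gives no mortality by group, and the studies in its Background conflict on whether levothyroxine is associated with mortality. The between-group effect is therefore a possibility and not a demonstrated error.

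Four further limits also stand:

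- Follow-up ending at death is stated for the cohort study only, so the same claim cannot be made outright for the emulation.
- The outcomes are incident diagnoses, so a fatal infarction or stroke that is coded would count as an event. Only deaths without a recorded event compete.
- The largest ratios come from extreme cases. With deaths at 20% per year, 1 − exp(−2) = about 86% of patients would die by year 10 from that hazard alone, leaving few at risk. Sixteen years is open only to patients who enter at the start of 2006. The protocol promises analyses by age band but does not say that curves will be drawn for each.
- The methods sentence is not exhaustive, and a full analysis plan may add cumulative incidence curves. Even so, Kaplan-Meier is the curve the article names, without distinguishing mortality from the other outcomes.

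**Conclusion.** The point holds as a low-cost improvement to a named method. In the cohort study, Kaplan-Meier curves for the cardiovascular and bone outcomes would overstate the proportion of patients with an event if read as absolute risk. The direction is certain once deaths are censored, and that censoring is inferred from the follow-up rule together with the outcome definitions.

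The size rests on assumed constant hazards. It is negligible over 5 years at low mortality (about 2% in relative terms with deaths at 1% per year), moderate at 10 years with deaths at 5% per year (about 26%), and more than double at 10 years with deaths at 20% per year. The sample size is unaffected, and nothing here casts doubt on the hazard ratios as cause-specific effects.

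**What to change.** In the Statistical analysis section:

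- For cardiovascular and bone outcomes, show Aalen-Johansen cumulative incidence curves with death as a competing event, in place of Kaplan-Meier curves.
- In the emulation, use the weighted version, and state how death is handled there.
- Keep Kaplan-Meier for all-cause mortality.
- Label the Cox hazard ratios for cardiovascular and bone outcomes as cause-specific, so that they are not read as ratios of risk.

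A sensitivity analysis of first event or death is optional.

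The cost is a wording change and slightly more analysis work with standard software. Date of death is already to be extracted. The displayed risks will be lower than Kaplan-Meier would have shown.
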